#### 12 month survey

All eligible women will be sent an SMS with an explanation of the survey and a link directly to the 12 month online survey, when their baby is 12 months of age. The online survey will be able to be completed on the woman’s mobile device. Women will have the opportunity to opt out, and there will be a reminder system in place, sending SMS reminders at 2 weeks and 4 weeks from the initial SMS.

The 12 month follow up will be a short online survey and will take approximately 10 min to complete. It will explore women’s parenting outcomes, their baby feeding and temperament as well as their emotional wellbeing and ongoing use of the kit (in the intervention arm) (Table 1).

### Data management and analysis

Survey data will be entered into the REDCap data management system [27]. All data will be then transferred to Stata version 14 [28] for data cleaning and analysis.

Data accuracy will be checked through several steps, including verification of the missing data, the range and format of values and checking consistencies and frequency distributions. Any missing or inconsistent values will be checked with the hard copy surveys.

In relation to the trial outcomes, trial arms will be compared using intention to treat analysis. Randomising the various clinic days is likely to result in groups that are evenly distributed - however analyses of study outcomes will be adjusted for baseline differences between the groups as needed. The first stage of the analysis will describe the demographic characteristics in the two trial arms using numbers and percentages, and these data will enable us to understand what factors we need to take into account in the analysis of outcomes. Study outcomes will be compared using χ^2^ and relative risks, with an additional multivariate analysis where there are differences in demographic characteristics of the women in the two trial arms. Comparison of means will be undertaken for continuous variables using t-tests where data are normally distributed or medians compared otherwise using Mann-Whitney U tests.

If the proportions of missing data are above 5%, several steps will be considered to handle missing data. The missing values will be first explored by trial arm and based on the characteristics of the missing data to identify if missing data are missing completely at random (MCAR), missing at random (MAR) or missing not at random (MNAR). Multiple imputation will be conducted considering reasons for and amount of missing data, availability of predictors of missingness and variables that are correlated with the incomplete variable. If the proportions of missing data are very large (more than 40%), only the results of the complete case analysis will be reported and the interpretative limitations of the trial results will be mentioned [29].

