### Randomisation and recruitment

The Women’s has four geographically-based maternity care teams, each of which has one antenatal clinic day per week (Monday - Thursday). To reduce the risk of contamination, (as would be the case if individual women were randomised), individual clinic booking days will be randomised, so that all women booking on a randomised day will receive the kit. Individual randomisation is not pragmatic given the high potential for clinician errors (clinicians would have to change the information they give to individual women throughout any booking clinic). Additionally, women may notice other women receiving different information packages.

Randomisation will be undertaken by an independent statistician at the Judith Lumley Centre. Using a blocked randomisation technique, the clinic days will be randomly allocated throughout the recruitment period to either intervention or standard care. The randomisation schedule will be kept confidential, with only the project coordinator, PhD student and senior research midwife having access in order to plan staffing for the research midwives.

As it is clusters (i.e. clinic days) being randomised and not individuals, randomisation will be done in advance, to ensure equal proportions of the four clinic days are randomly allocated to standard care and the intervention over the estimated 22 week recruitment period. The recruitment period was predicted based on the average number of booking visits per week at the Women’s and an estimation of women’s eligibility. For various reasons (e.g. geographical variations in the number of women meeting eligibility criteria), some clinic days may meet their quota of eligible women in fewer recruitment days than others. For this reason, recruitment will cease in each clinic (maternity care team) when their quota is reached.

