### Sample size

The experience of motherhood questionnaire (EMQ), a 20-item self-report measure, has been used to determine the sample size [18] with the goal of reducing the proportion of women scoring low on the EMQ. A score of 40 on the EMQ is a typical median score for a sample of first time Australian mothers. We therefore expect 50% of women in the standard care to score 40 or less. To detect a difference of 10% (50% compared to 60%) scoring 40 or less between new mothers who have received the kit and those who have not would require 408 per group (total of 816 women) with 95% confidence and 80% power. Allowing for loss to follow up we therefore aim to recruit 1000 mothers. We do not anticipate needing to allow for any potential effect of clustering given we will ensure relatively equal numbers of women from the four geographically-based teams (i.e. the main factor which may introduce differences) will be allocated to both trial arms. Similarly, the clinical guidelines, models of care, and appointment length are all uniform across the four teams, thus minimising the potential for different influences based on team allocation. Where appropriate, we will adjust for demographic and birth outcomes.

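### Clinic days are balanced within the four maternity teams, but the stated comparisons leave team out; including it is a small, nearly free gain in precision

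*Protocol article*

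**What the plan says.** Under Randomisation and recruitment, the protocol article describes "four geographically-based maternity care teams, each of which has one antenatal clinic day per week (Monday - Thursday", so team and weekday are the same factor. The unit allocated is the day: "individual clinic booking days will be randomised, so that all women booking on a randomised day will receive the kit". The schedule is blocked and drawn up beforehand "to ensure equal proportions of the four clinic days are randomly allocated to standard care and the intervention over the estimated 22 week recruitment period". Recruitment stops in each team once that team reaches its quota.

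The Sample size section relies on this balance as its reason for making no allowance for clustering. It says of the four teams: "i.e. the main factor which may introduce differences) will be allocated to both trial arms". It promises only relatively equal numbers of women by team, and it names demographic factors and birth outcomes as possible adjusters.

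The section on Data management and analysis then fixes the comparisons: "Study outcomes will be compared using χ^2^ and relative risks, with an additional multivariate analysis where there are differences in demographic characteristics of the women". Continuous scores are compared by t-test or Mann-Whitney test. A more general sentence allows adjustment for baseline differences when needed. No sentence in the analysis or sample size text enters team as a stratum or covariate.

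**The concern.** Team restricts the randomisation, and the article itself treats it as the most likely source of differences. An analysis normally carries such a factor, because balancing on it removes between-team variation from the treatment contrast. A test that ignores team leaves that variation in the standard error.

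The adjustment rule does not repair this. It is triggered by differences seen between arms, and a factor balanced by design will rarely show one. The rule also makes the adjustment depend on the data.

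Balancing days does not guarantee balance in women. Eligible numbers per day vary, teams can stop early at their own quotas, and post-randomisation exclusions and non-response come later. At stake is some precision on the primary outcome, the proportion scoring 40 or less on the EMQ, and on the other between-arm comparisons.

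**Working it through.** **Inputs from the article.** 50% v 60% scoring 40 or less; 95% confidence (taken as two-sided alpha 0.05); 80% power; 408 per group; four teams; 22 weeks.

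**Inputs assumed.** Control rates by team, averaging 50%, because none are given; 408/4 = 102 women per team per arm; a 10-point effect in every team; no within-day correlation, so that the team question stands alone.

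**Step 1: the article's own figure.** n = [1.96·√(2·0.55·0.45) + 0.8416·√(0.5·0.5 + 0.6·0.4)]² / 0.10² = (1.379 + 0.589)² / 0.01 = 387.3, so 388 per group. With continuity correction, (387.3/4)·[1 + √(1 + 4/(387.3·0.10))]² = 407.1, so 408. The stated size is reproduced, with no team term in it.

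**Step 2: team mix exactly balanced.** With P₀ and P₁ the arm means, p₀ₖ and p₁ₖ the team rates, and n = 102:

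- team ignored: SE = √{[P₀(1−P₀) + P₁(1−P₁)] / 4n}
- team stratified: SE = √{Σ[p₀ₖ(1−p₀ₖ) + p₁ₖ(1−p₁ₖ)] / (16n)}

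| Assumed control rates by team | SE ignored | SE stratified | Ratio | True alpha, team ignored | Power ignored v stratified |
|---|---|---|---|---|---|
| 45, 48, 52, 55% | 0.0347 | 0.0346 | 1.003 | 0.049 | 82.3% v 82.5% |
| 40, 45, 55, 60% | 0.0347 | 0.0342 | 1.013 | 0.047 | 82.6% v 83.2% |
| 35, 45, 55, 65% | 0.0347 | 0.0338 | 1.027 | 0.044 | 82.9% v 84.2% |
| 30, 40, 60, 70% | 0.0347 | 0.0328 | 1.055 | 0.039 | 83.6% v 86.1% |

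In simulation with balanced teams, the unadjusted risk difference averaged 0.0997 to 0.1001 for a true 0.10, so there is no bias.

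**Step 3: team mix varying by chance.** Let the number of women per team per arm be Poisson with mean 102. The mix then adds variance 2·V/408 to the unadjusted difference, where V is the variance of the four team rates.

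- 40-60%: V = (0.10² + 0.05²)/2 = 0.00625, so the SD from mix is √(2·0.00625/408) = 0.0055, or 0.55 points.
- 30-70%: V = (0.20² + 0.10²)/2 = 0.025, so the SD from mix is 0.0111, or 1.1 points.

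Under no effect the stratified SE at 30-70% is 0.0332, and √(0.0332² + 0.0111²) = 0.0350. This equals the unstratified SE, √(2·0.25/408) = 0.0350. The usual standard error therefore already covers chance variation in mix. Simulation agrees: the ratio of unstratified SE to true SD is 0.998 to 1.002, and type I error is about 5%. What is lost is power: about 0.7 points at 40-60%, 1.8 at 35-65% and 3.3 at 30-70% (repeat runs gave up to 3.7 at the widest spread). At 45-55% the difference is negligible.

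**Step 4: how far one realised imbalance could move the estimate.** Shift = Σ(w₁ₖ − w₀ₖ)·pₖ, with w the team shares. Suppose the two extreme teams' shares each move 2 percentage points, in opposite directions in the two arms. At 40-60% the shift is 0.04·(0.60 − 0.40) = 0.8 points. At 45-55% it is 0.4 and at 30-70% it is 1.6. This illustrates one possible draw lined up with the rates. It is not an expected bias.

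**The case against.** A reader might infer that team differences remain in the estimated kit effect. The documents do not support that. With days balanced within teams, the unadjusted estimate is unbiased, and chance drift in numbers gives error around zero that the usual standard error already covers. Nor can the two harms be added: the standard error is too large only if mix is balanced, and mix adds noise only if it is not.

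It can also be said that the Sample size section describes guidelines, models of care and appointment length as uniform across teams, that nothing supports a 40-point spread between teams, and that the general sentence on baseline differences would permit adjustment for team. The first two points stand as reasons to expect a small effect. But uniform care does not make geographically defined populations alike, and the article itself mentions geographical variation in eligibility. The third is a permission, not a commitment, and it depends on what is observed.

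A full covariate list may well sit in an analysis plan that is not shown. The point here is narrower: the article does state the tests and the adjustment rule, and as stated they omit the factor on which allocation was balanced.

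**Conclusion.** The point holds in a limited form. Allocation is balanced by team, the article calls team the main possible source of differences, and the stated analysis does not use it. The cost is a standard error about 0.3% to 1% too large for assumed team rates of 45-55% to 40-60% (about 5% at 30-70%) if mix is balanced. If mix varies by chance, the cost is about 0.7 to 3.3 points of power at 40-60% to 30-70%. If teams are alike, nothing is lost. All of this rests on assumed team rates and on 102 women per team per arm.

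It should not be read as showing that the trial's test is conservative overall. The day is the randomised unit, and ignoring correlation within it works the other way. With 22 × 4 = 88 days and 816/88 = 9.3 analysed women per day, an assumed intracluster correlation of 0.01 to 0.05 gives a design effect, 1 + 8.27·ICC, of 1.08 to 1.41 and a true alpha of 0.060 to 0.099. That is a separate and larger matter, which a team term does not resolve.

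**What to change.** In Data management and analysis, state that every between-arm comparison, primary and secondary, includes maternity care team as a four-level factor whether or not baseline differences are observed.

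- **EMQ of 40 or less and other binary outcomes:** a Mantel-Haenszel relative risk stratified by team, or a log-binomial or modified Poisson model with arm and team.
- **Continuous scores:** linear regression with arm and team in place of the unstratified t-test. Where a rank test is kept, use its team-stratified form.

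Any further covariate adjustment can be added to this. Accounting for the clinic day as the randomised cluster must be specified as well.

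The cost is a sentence or two of wording and three model degrees of freedom among about 816 women. Team is known from the booking clinic, so no new data are needed, and the sample size does not rise on this account.

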
**Table 1 Tab1:** Data collection for the evaluation

	2 month survey	6 month interview	Partner survey	12 month survey
Views of the care and information received during pregnancy, birth and postnatal	X	X	X	
Views and experiences of the Growing Together kit (intervention)	X	X	X	X
Experience of motherhood – EMQ [18]		X		
Parental emotional wellbeing - EPDS [19] & K6 [20]	X	X	X	X
Health-seeking for baby’s or mother’s wellbeing		X		
Developmental, emotional and physical health of infant (e.g. infant feeding; infant sleeping; infant temperament [21])		X		X
Parents’ knowledge and confidence [22]		X	X	X
Parenting behaviour and parent-child interactions [21, 23]		X	X	X

‘Parenting self-efficacy’ will be measured using a single item global rating of the parent’s perception of themselves as being a ‘good’ parent, ranging from ‘1’ being a ‘not very good’ parent to ‘5’ being a ‘very good’ parent [22].

‘Parental responsiveness/warmth’ will be measured using six items from the Child Rearing Questionnaire [25] (scoring from 1 to 5), assessing parents’ expression of warmth, affection and enjoyment with the child [23]. ‘Irritable parenting’ will be measured using five items from Parental Perceptions and Behaviours Scale [26] (scoring from 1 to 5) about frequency of parental anger and irritability toward the child [23].

For these measures, item scores will be summed and then averaged making a total score ranging from 1 to 5 with higher scores indicating higher levels of responsiveness and irritability. Previous research reports internal consistency coefficients of .86 and .87 respectively when used with Australia mothers of infants and young children [21]. ‘Activities with child’ measures the extent to which parents engage in activities with their baby which are likely to support baby development. This will be assessed with four items, asking the frequency of activities with a baby in a typical week, rated on a 4-point scale from 1=‘not at all’ to 4 = ‘every day’ ((α = .71) [21].Parents’ views and experiences of the care and information received during pregnancy, birth and postnatal period.Parents’ views and experiences of the *Growing Together* kit and its usefulness (intervention arm only).Respondents’ background characteristics will also be collected in all surveys and interviews.

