### Ethical considerations

Given clinic days will be randomised, individual consent will not be sought; rather potential respondents will be informed as described below.

When the first survey (at 2 months postpartum) is mailed out, the cover letter will explain that the Women’s is interested in evaluating the information they provide to prospective and new parents. It will explain that as part of the evaluation, women will be sent a survey, will be contacted at 6 months post-birth for a short telephone interview and then will be sent a final survey 12 months after the birth. The letter will also explain that they will receive a postal survey for partners to complete at around 6 months. If women prefer not to be involved they may complete an ‘opt out’ form. We will consider return of the surveys as ‘consent’, and if women do not opt out they will be included in the ongoing follow up.

The cover letter will explain that JLC has been engaged to undertake the work, and that the surveys have been sent by the Women’s Hospital (to reassure women regarding any privacy concerns). The cover letter will include contact details for research team if parents have any questions or would like to discuss the study. For women who choose to opt out of receiving further follow up, they will be able to send the opt out form back to a Women’s staff member via a pre-addressed reply paid envelope, and their contact details will be removed from the survey mail out list. For women who wish to participate, they will be able to return their completed survey in a pre-addressed, reply paid envelope to the research team.

We prefer this ‘opt out’ method as opposed to an ‘opt in’ given our knowledge of the response rates to postal surveys among similar women – often 30 to 40% in surveys we have conducted at the Women’s [30] and elsewhere in Victoria [31]. If we required women to ‘opt in’, the chance of having this percentage of respondents would probably be even lower, and thus diluting the generalisability of the findings. Participants will not be offered any type of incentives for completion of the surveys.

Prior to sending out the surveys after the birth, we will check that only women who are discharged with a live baby are on the list. Where women have a known antenatal or neonatal loss they will be excluded, and women’s contact details will be removed from the survey mail out list.

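### Above 40% missing, the plan reports complete cases and nothing else; the protocol's own past postal response (30–40%) makes this the likely case for the 2-month survey, and possibly the partner survey

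*Protocol article*

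**What the plan says.** The missing-data rules are in the last paragraph of Data management and analysis, and they work in tiers.

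- **Over 5%:** "If the proportions of missing data are above 5%, several steps will be considered to handle missing data". Exploration comes first: "The missing values will be first explored by trial arm and based on the characteristics of the missing data", with the stated aim "to identify if missing data are missing completely at random (MCAR), missing at random (MAR) or missing not at random (MNAR"). Imputation follows: "Multiple imputation will be conducted considering reasons for and amount of missing data, availability of predictors of missingness", together with variables correlated with the incomplete one.
- **Over 40%:** "If the proportions of missing data are very large (more than 40%), only the results of the complete case analysis will be reported". The only accompaniment is that "the interpretative limitations of the trial results will be mentioned".

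The same section says that the arms are compared by intention to treat.

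Ethical considerations defends opt-out follow-up by citing postal response among similar women, "often 30 to 40% in surveys we have conducted", and adds that opt-in would probably do worse than that.

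According to Data collection and Table 1, the postal instruments are the 2-month women's survey and the 6-month partner survey, each with an online option. The EMQ appears only in the 6-month telephone interview. The 12-month survey is online, by SMS link.

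**The concern.** The plan does most about missing data when the problem is moderate and least when it is severe. At 39% missing it would impute. At 41% it would show one analysis of those who replied and add a caveat. The word *only* excludes imputation and also any analysis showing how far the result depends on the women who did not reply.

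If response to the postal surveys resembles the figure the article cites, the tier meant for the exceptional case becomes the usual one for those surveys. A comparison labelled intention to treat would then rest on a minority who chose to reply, and the reader could not judge its robustness.

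Non-response could plausibly differ by arm. Implementation of intervention gives intervention women extra contacts (an App reminder after booking, and a letter and sticker after the birth). The documents do not show that it will differ.

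A smaller fault lies beside this one. Exploring observed data can produce evidence against MCAR, but it cannot separate MAR from MNAR. The exploration step therefore cannot do what it is said to do, and this is the reason a sensitivity analysis is needed.

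**Working it through.** **Inputs**

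| Input | Value | Where |
|---|---|---|
| Trigger for complete cases only | more than 40% missing | Data management and analysis |
| Past postal response, similar women | often 30–40% | Ethical considerations |
| Evaluable / recruited | 816 / 1000 | Sample size |
| EMQ design contrast | 50% v 60% | Sample size |
| Mode of EMQ collection | telephone, 6 months only | Table 1; 6 month telephone interview |

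**1. The plan's own figure.** Two proportions, 50% v 60%, two-sided 5% (taken from the stated 95% confidence), 80% power, pooled variance: 388 per group without continuity correction and 408 with it. The stated 408 per group (816) is reproduced with the correction. Implied loss allowance = 1 − 816/1000 = 18.4%.

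**2. Postal surveys against the trigger.** Missing share = 1 − response.

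- 30% response: 70% missing, 30 points over the trigger.
- 40% response: 60% missing, 20 points over.
- To escape the rule, response must be at least 1 − 0.40 = 60%.

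If 1000 women were surveyed, 300–400 would reply, about 150–200 per arm.

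**3. Primary outcome against the trigger.** At the implied loss of 18.4% the EMQ is well below 40%. It crosses only if fewer than 60% are interviewed. The documents give no telephone response rate.

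**4. What complete-case reporting can hide (illustration only).** Let r be the response share, taken as equal in both arms, D_R the arm difference among responders and D_N that among non-responders. Then

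D_all = r × D_R + (1 − r) × D_N.

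Take D_R = 10 points. This size is borrowed from the EMQ design contrast for scale; it is not a forecast for any postal outcome.

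| Response r | D_all if D_N = 0 | D_all if D_N = −5 | D_N that cancels the effect, −r × 10/(1 − r) |
|---|---|---|---|
| 30% | 3.0 | 0.3 × 10 − 0.7 × 5 = −0.5 | −4.3 |
| 40% | 4.0 | 0.4 × 10 − 0.6 × 5 = 1.0 | −6.7 |

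In tipping-point terms, write each arm's non-responder proportion as its responder proportion plus a shift δ. Then D_all = D_R + (1 − r)(δ_kit − δ_standard). The effect reaches zero when the shifts differ by −10/0.7 = −14.3 points at 30% response, or −10/0.6 = −16.7 points at 40%. These agree with the table: 10 − 14.3 = −4.3 and 10 − 16.7 = −6.7.

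**5. What *missing data* covers.** The section does not define it.

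- *Unreturned surveys included.* The 2 month survey section classes a non-returner as lost to that follow-up, and an intention-to-treat comparison concerns everyone allocated. Steps 2 and 4 then apply.
- *Blank items in returned surveys only.* The 40% tier would rarely be reached, but the article would then state no handling for unreturned surveys.

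**The case against.** **The cited rate is not a forecast.** The 30–40% describes earlier surveys and is used to justify opt-out. This trial adds an online option, a reminder card and a second mailing. That stands as a caution, so the rule is likely to apply, not certain. Response would still have to reach 60%, and nothing in the article supports such a rise. For partners no rate is given, so that part is conditional.

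**The primary outcome.** A reader might infer that the EMQ will also be reported on a self-selected minority, and that 60% v 50% would shrink to 3–4 points. The documents do not support this. No postal survey measures the EMQ, and interview attempts run for three months with number look-up and an SMS. The allowance is 18.4%.

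**No predictors.** A reader might infer from "background characteristics will also be collected in all surveys and interviews" that a woman who never replies has almost nothing to impute from. That goes too far. Clinic day and due date are held for every eligible woman, birth outcomes are checked in hospital systems, and 2-month non-responders who do not opt out remain in later waves, where EPDS/K6 is measured again.

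**Imputation at 60–70% missing is doubtful.** This is fair. Imputation under MAR would also not remove the bias illustrated above if response depends on the unseen outcome. It is an argument for a tipping-point analysis, which needs no good predictors, and not for reporting nothing further.

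**It belongs in the analysis plan.** The choice of sensitivity method does. The word *only* does not: it is a rule stated here, and a later plan adding a sensitivity analysis would contradict it. The rule cites a source not available to this review, but the citation does not change what the rule does.

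**Conclusion.** The concern holds for the postal secondary outcomes. If missing data include unreturned surveys and response resembles the cited 30–40%, missingness is 60–70%. The 2-month women's survey then falls under a rule that forbids reporting any alternative to complete cases. The partner survey does too if partners respond similarly. What is affected is views of care, EPDS/K6 at those contacts, and partner confidence and parenting behaviour.

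The size of any bias is unknown. The figures of 3–4 points remaining, and of −4.3 or −6.7 points cancelling the effect, assume a 10-point responder difference and equal response in both arms. They show sensitivity and predict nothing. The primary EMQ is outside the rule unless fewer than 60% are interviewed.

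The change is worth making because it is cheap and determines what can be concluded from these surveys. It does not call the trial's primary comparison into question.

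**What to change.** In Data management and analysis:

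1. Replace the 40% sentence with wording such as: *Complete-case results will be reported for every outcome. At any level of missingness, including above 40%, they will be accompanied by a sensitivity analysis that shifts the outcomes of non-responders separately in each arm and reports the shifts at which the conclusion changes. Where feasible, an analysis assuming missing at random will be added, using clinic day and team, birth data and other survey waves.*
2. State whether the proportion missing counts unreturned surveys, blank items or both.
3. Reword the exploration step so that it describes missingness by arm and characteristics and looks for evidence against MCAR, without claiming to identify MNAR.

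The cost is a little analysis time. The tipping-point analysis needs no new data, and no new extraction on women who did not reply is proposed. Before birth data are used in the missing-at-random analysis for women who returned nothing, the team should check that the existing approval covers it, because consent is taken from survey return. Conclusions for the postal outcomes may look less firm, as they should if they depend on who replied.
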